## Abstract

**Background:**

The World Health Organization’s End TB Strategy envisions a world free of tuberculosis (TB)—free of deaths, disease, and suffering due to TB—by 2035. Nonadherence reduces cure rates, prolongs infectiousness, and contributes to the emergence of multidrug-resistant TB (MDR-TB). Moreover, MDR-TB is a growing, complex, and costly problem that presents a major obstacle to TB control. Directly observed therapy (DOT) for treatment adherence monitoring is the recommended standard; however, it is challenging to implement at scale because it is labor-intensive. Mobile health interventions can facilitate remote adherence monitoring and minimize the costs and inconveniences associated with standard DOT.

**Objective:**

The study aims to evaluate the effectiveness of using video directly observed therapy (VDOT) plus incentives to improve medication adherence in TB treatment versus usual-care DOT in an African context.

**Methods:**

The DOT Selfie study is an open-label, randomized controlled trial (RCT) with 2 parallel groups, in which 144 adult patients with TB aged 18-65 years will be randomly assigned to receive the usual-care DOT monitoring or VDOT as the intervention. The intervention will consist of a smartphone app, a weekly internet subscription, translated text message reminders, and incentives for those who adhere. The participant will use a smartphone to record and send time-stamped encrypted videos showing their daily medication ingestion. This video component will directly substitute the need for daily face-to-face meetings between the health provider and patients. We hypothesize that the VDOT intervention will be more effective because it allows patients to swallow their pills anywhere, anytime. Moreover, patients will receive mobile-phone–based “social bundle” incentives to motivate adherence to continued daily submission of videos to the health system. The health providers will log into a secured computer system to verify treatment adherence, document missed doses, investigate the reasons for missed doses, and follow prespecified protocol measures to re-establish medication adherence. The primary endpoint is the adherence level as measured by the fraction of expected doses observed over the treatment period. The main secondary outcome will be time-to-treatment completion in both groups.

**Results:**

This study was funded in 2019. Enrollment began in July and is expected to be completed by November 2020. Data collection and follow-up are expected to be completed by June 2021. Results from the analyses based on the primary endpoint are expected to be submitted for publication by December 2021.

**Conclusions:**

This random control trial will be among the first to evaluate the effectiveness of VDOT within an African setting. The results will provide robust scientific evidence on the implementation and adoption of mobile health (mHealth) tools, coupled with incentives to motivate TB medication adherence. If successful, VDOT will apply to other low-income settings and a range of chronic diseases with lifelong treatment, such as HIV/AIDs.

**Trial Registration:**

ClinicalTrials.gov NCT04134689; http://clinicaltrials.gov/ct2/show/NCT04134689

**International Registered Report Identifier (IRRID):**

DERR1-10.2196/18029

## Introduction

The World Health Organization’s End TB Strategy envisions a world free of tuberculosis (TB)—free of deaths, disease, and suffering due to TB—by 2035 [1]. In 2018, TB killed an estimated 1.5 million people, with 10 million new cases of the disease worldwide [2]. Nonadherence to medication is a common, complex, and costly problem, which hampers TB control [3]. It reduces cure rates, prolongs infectiousness, and contributes to the emergence of multidrug-resistant TB (MDR-TB) strains [4-7].

MDR-TB is on the rise, with an estimated 580,000 cases reported worldwide in 2018 [2] compared to 480,000 in 2014 [8]. The World Health Organization (WHO) and the Centers for Disease Control and Prevention (CDC) recommend directly observed therapy (DOT) for TB treatment to monitor and provide treatment support for affected people whenever feasible [9,10]. When implemented properly, DOT fosters high levels of treatment adherence and early detection of adherence problems, adverse drug reactions, and worsening TB symptoms [9].

The WHO estimates that approximately 50% of patients who start treatment often fail to adhere to their prescribed medication regimens, particularly in low- and middle-income countries [11]. However, DOT is difficult to implement in low-resource settings such as Africa. Major barriers that hinder the effectiveness of DOT are TB stigma, patients forgetting to meet with TB providers or treatment supporters, the inconvenience of daily face-to-face meetings, high costs of travel, insufficient capacity of the public health workforce, and long patient waiting times at health facilities [12,13]. Therefore, innovative ways to overcome these barriers are urgently needed.

Mobile health (mHealth) tools have shown promise as alternative interventions to in-person DOT [14-16]. For example, SMS text messages and real-time electronic monitors have been used to improve adherence to antiretroviral treatment in Uganda [17]. Video directly observed therapy (VDOT) that uses a smartphone app to record videos of medication intake presents a novel way to monitor adherence remotely and overcome health system barriers of treatment delivery [18,19]. VDOT enables patients to submit videos showing daily medication intake for observation by TB care providers without the need to meet in-person. Only a few published observational studies have evaluated VDOT, including 2 from Africa [19-24]. One pilot study from Kenya showed video observed therapy to be both technically feasible and acceptable to patients and health professionals [23]. Similarly, a recent pilot done in Uganda showed VDOT to be feasible and acceptable to patients for the monitoring and support of TB treatment [24]. The efficacy of VDOT has been evaluated in 3 randomized controlled trials (RCTs) in the United States, United Kingdom, and Moldova, which have shown it to be feasible, acceptable, cost-saving, and convenient to patients [25-27]. However, to our knowledge, no published RCTs comparing VDOT to usual care have been reported in Africa.

The current study will adapt an existing VDOT platform and a smartphone app that was developed by researchers at the University of California in San Diego, California, United States [18], to suit the African context. Specifically, we will translate SMS text reminders and social bundle incentives to motivate adherence. Using mHealth tools in a context-specific way is expected to promote effective patient self-management and improve patient-provider interactions. Mobile technology has the potential to facilitate greater patient reach, anonymity, information dissemination, as well as the implementation of interventions and services in diverse contexts and settings [28,29]. Upon successful completion of this trial, we expect our findings to contribute to evidence that informs the adoption and scale-up of VDOT for use in low-income countries.

## Methods

### Trial Design

The DOT Selfie study is an open-label RCT. A total of 144 adult patients with a confirmed diagnosis of drug-susceptible TB who are initiating treatment or are within 1 month of treatment initiation at designated TB clinics will be randomized into 2 parallel groups. Of the 144 participants, 72 will be randomized into a control group to receive the usual-care DOT (UC-DOT), and 72 will be randomized into the intervention group to receive a smartphone with the VDOT app to video-record daily medication intake for review via a secure cloud system. All study participants will attend 2 monthly clinic visits at 2, 4, and 6 months (or at the end of treatment), during which clinical and sputum assessments will be performed.

### Eligibility Criteria

Participants will be included if they are (1) new or retreatment patients with clinically or microbiologically confirmed TB who initiated treatment within 1 month (we chose to enroll both new and retreatment cases since adherence barriers exist in both groups), (2) aged 18 to 65 years, (3) planning to reside in Kampala, Uganda, for the entire period of 6 months while on treatment to facilitate close follow-up, (4) able to provide signed informed consent, and (5) able to speak and read English or Luganda (the local dialect). Participants will be excluded if they (1) are confirmed to have drug-resistant TB (MDR- or XDR-TB); (2) are very ill patients (ie, those who feel that they would not be able to withstand 2 hours of study procedures at enrollment; (3) have a cognitive, motor, visual, or hearing disability that prevents full participation in VDOT (eg, disabilities that prevent holding a phone or an inability to swallow medication as whole pills); and (4) do not have access to a power source to charge the smartphone or reside in areas without cellular network coverage.

### Study Setting and Recruitment

The primary study site will be the Lubaga TB clinic in Kampala, Uganda. Other public clinics, such as Kawala, Kitebi, or Kisenyi, which provide free TB services, will be used as secondary sites to supplement study recruitment. The study clinic sites are all located about 10-15 km from Kampala city center and, together, treat approximately 1000 TB patients annually. We estimate that a total of 8-10 patients per week, or 32-40 patients per month, will be enrolled by the research team. Since the selected sites treat roughly 90-100 TB patients a month, we will use consecutive sample selection to enroll every eligible subject in each arm until the required sample size is achieved. With this recruitment rate, we expect to complete participant enrollment within 4-5 months. The primary recruitment strategy is to screen patients who are newly diagnosed or those that will visit the clinic within the first month of their treatment. Eligibility will be assessed by a trained research assistant who will describe the study to the eligible patient and answer any study-related questions. Patients who are interested in participating will be required to provide written consent, after which they will be invited to complete a baseline questionnaire (Multimedia Appendix 1). The baseline questionnaire will ask questions about (1) patients’ TB diagnosis and initial treatment; (2) socio-demographics and income; (3) experience with cellphones, smartphones, and technology; (4) transportation and other costs; (5) social and personal life; (6) knowledge of TB disease and treatment; (7) privacy and confidentiality concerns; (8) current family and friend support; and (9) perceived stigma from the community. All participants will be educated on TB, including treatment, side effects, and the need for adherence. Thereafter, they will be randomized to one of 2 groups. The participant flow is described in Figure 1.

**Figure 1 figure1:**
[figure not shown]
DOT Selfie participant flow diagram. DOT: directly observed therapy; MDR-TB: multidrug-resistant tuberculosis; TB: tuberculosis; VDOT: video directly observed therapy; XDR-TB: extremely drug-resistant tuberculosis.

### Study Procedures

#### Randomization

We will randomize 144 participants with an equal allocation ratio of 1:1 to receive either VDOT or UC-DOT. An equal allocation was chosen to optimize the power of the study [30]. Permuted block randomization with block sizes of 4 and 6 will be used to allocate participants to intervention or control groups while maintaining balance across groups. Each block will have a specified number of randomly ordered treatment assignments [30]. Additionally, stratified randomization will be done according to sex to ensure equal representation of men and women in each study group [30]. The stratification is justified because sex is an important variable that influences adherence to TB treatment [31]. A computer program will randomly generate study arm assignments within block sizes of 4 and 6. This randomization will minimize the likelihood that the study team will be able to predict the next study arm assignment. Each block will contain equal proportions of control and intervention. Within each block will be 4 or 6 sealed, opaque allocation envelopes, depending on the block size. Blocks and allocation envelopes will be sequentially numbered according to the computer-generated randomization schedule. Each allocation envelope will contain an assignment card on which the study group assignment (UC-DOT or VDOT) will be printed. To assign a patient to a study group, blocks will be selected in their sequential order. Allocation envelopes within them will be selected sequentially as well. Each envelope will be opened only after the participant details have been written on it. Carbon paper inside the envelope will transfer participants’ details to the assignment card. Allocation envelopes will be sealed using tamper-proof security tape.

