#### Control: Usual-Care Directly Observed Therapy (UC-DOT)

Participants will receive UC- DOT as administered in routine clinical practice under the Uganda National TB program. Routine DOT typically involves treatment observation 3-5 times per week by a designated treatment supporter who could be a trained community worker, a volunteer lay-worker, a family member, a friend, or community linkage facilitator, with the weekend doses self-administered. The name and phone contact details of each designated treatment supporter for each patient are documented. The treatment observation and support occur at any location mutually agreed upon between the patient and their treatment supporter. To document adherence, the patient records daily doses taken on a predesigned treatment card issued at the clinic and returns it at every routine visit. Adherence is further assessed using patient self-reports, pill counts, and clinic attendance for prescription refills. Study research assistants will work in partnership with designated treatment supporters to collect study information on adherence from clinic records coupled with a structured adherence questionnaire at follow-up visits. Patients in the UC-DOT control group will be followed up for missed doses and routine visits according to the National TB program guidelines. Research staff will only follow up with participants for scheduled study visits and procedures.

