### Sample Size

This trial is powered on the primary outcome measure and based on a comparison of the medication adherence level between the UC-DOT group and the VDOT group. The calculated sample size is 124 in order to achieve a chi-square test difference of 0.85 versus 0.63 (difference 0.22 and odds ratio 0.30) between the groups. We assumed an attrition rate of 14%, guided by published literature; this was based on a randomized controlled trial comparing a digital adherence intervention and usual care in Kenya in which the overall loss to follow-up rate was 11.7% (9.9% in the usual-care DOT arm and 1.76% in the digital intervention arm) [38]. By inflating the attrition rate to 14%, we erred on the higher side of attrition. In contrast, another RCT of asynchronous VDOT done in the United Kingdom had a higher attrition rate of 23%; however, the study population was very different from our current study in that it included 58% of homeless subjects [15]. At a 14% attrition rate, the estimated final sample size was 144 participants with 72 subjects per group. This would provide a power of 80% to detect a 22% difference in the primary outcome between the 2 comparison groups (85% VDOT vs 63% DOT) based on a 2-sided significance level of 5%. Sample size tables were used to estimate precision. All calculations were performed using the SAS statistical software package (version 9.3; SAS Institute).

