Univariate statistics will be used to describe the baseline characteristics of the study population, the prevalence of individual clinical responses, and the level of adherence. Similar analyses will be repeated for secondary outcomes. Multivariable logistic regression analyses will be done to test for significant associations between study groups (VDOT/ UC-DOT) as the main exposure and the primary binary outcome of adherence (≥80%; yes/no). Age and HIV status are set a priori as potential confounders that will be adjusted for in all the models. Sex will not be adjusted since the randomization is stratified by sex. Other covariates that will be adjusted for in the models include education level, income, and smartphone ownership, previous TB treatment, HIV status, and other clinical variables at baseline. Crude and adjusted odds ratios with 95% confidence intervals will be presented, and statistically significant *P* values will be less than .05.

Secondary analyses of time-to-treatment completion will provide another outcome that can be used to compare the 2 groups according to TB program performance indicators. Survival analysis to compare the median time-to-treatment completion between study groups with associated log-rank tests will be performed. Crude and adjusted Cox proportional hazards regression analyses will be performed to determine factors associated with time-to-treatment completion. Cox proportional hazards ratios with corresponding 95% confidence intervals will be presented. Other analyses comparing trends at months 2, 4, and 6 in adherence, sputum conversion, and clinical response will be performed. These repeated measures data will be modeled as a discrete-time Markov chain or Poisson process [30]. Analyses will be done using Stata (version 14; StataCorp) and R (version 3.3.2; R Core Team) software.

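### Clinic is neither a randomization stratum nor a listed covariate, although several clinics recruit and routine DOT is the control: a cheap gain in precision is left unused, with no bias

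*Protocol article*

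**What the plan says.** Study Setting and Recruitment names one primary clinic and then adds: "Other public clinics, such as Kawala, Kitebi, or Kisenyi, which provide free TB services, will be used as secondary sites to supplement study recruitment". The number of secondary clinics and their expected shares of the 144 patients are not fixed.

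The control is not a study-delivered procedure: "Participants will receive UC- DOT as administered in routine clinical practice under the Uganda National TB program". The same section allows 3-5 observations a week by any of several kinds of supporter. Study staff collect control adherence from clinic records together with a structured questionnaire.

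Randomization uses permuted blocks of 4 and 6, with one stratification factor: "Additionally, stratified randomization will be done according to sex to ensure equal representation of men and women in each study group". The reason given is that sex influences adherence.

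Statistical Analyses compares mean FEDO between arms with a Welch t test and no covariates. For binary adherence (FEDO of at least 80%) it plans logistic regression: "Age and HIV status are set a priori as potential confounders that will be adjusted for in all the models". The other named covariates are education, income, smartphone ownership, previous TB treatment and further baseline clinical variables. Sex is left out because it is a stratum. Clinic is not mentioned.

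**The concern.** The plan's reason for stratifying by sex, that it influences adherence, could apply equally to clinic. Clinics may differ in how routine DOT is run, how missed doses are followed up and how completely records are kept. The control arm depends on all three. If clinics do differ, a trial of 144 patients can by chance end with a different clinic mix in the two arms. Part of the observed difference in adherence would then reflect clinic. As described, neither the randomization limits that imbalance nor the analysis corrects for it.

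At stake are precision and the credibility of a result that might show a visible clinic imbalance. The validity of the test is not in question. The planned power leaves little to spare, so a nearly free gain is worth considering.

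**Working it through.** **1. The plan's own figures.** Inputs from Sample Size: 0.85 versus 0.63, 80% power, two-sided 5%. The pooled-variance formula for two proportions without continuity correction gives 62 per arm, or 124 in total. This matches "The calculated sample size is 124 in order to achieve a chi-square test difference of 0.85 versus 0.63". Power at 62 per arm is 80.5%. Allowing for 14% attrition, 124/0.86 = 144.2, against the stated 144. Nothing below changes N.

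**2. Assumptions that the protocol does not supply.** Four clinics with shares 1/2, 1/6, 1/6, 1/6; 72 patients per arm; a gap g in adherence between the primary clinic and the others of 20, 25 or 35 points; 60% men in the simulations.

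**3. How far clinic mix can drift with sex-only strata.** With 72 of 144 patients at the primary clinic, the number on VDOT there is close to hypergeometric:
- variance = 72 × 0.5 × 0.5 × 72/143 = 9.06, so SD 3.01 patients, or 4.2% of 72;
- 95% range = 50% ± 1.96 × 4.2%, or about 42-58%.

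For a secondary clinic with 24 patients:
- variance = 24 × 0.25 × 120/143 = 5.03, so SD 2.24 patients, or 9.3% of 24;
- 95% range about 32-68%.

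Simulation with blocks of 4 and 6 within sex agrees. Across three sets of assumed shares (50/17/17/17, 70/10/10/10 and 25 each), the chance that at least one clinic's share differs between arms by more than 10 points is 24-45%. With sex-by-clinic strata, none of 6000 runs per scenario exceeded 10 points.

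**4. What that does to the arm difference, if the gap applies in both arms.** The SD of the between-arm difference in the primary clinic's share is √(0.25 × 2/72) = 0.083. The chance shift has SD g × 0.083:

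| Gap g | SD of shift | 1.96 × SD | Simulated 95th percentile of absolute shift |
|---|---|---|---|
| 20 points | 1.7 | 3.3 | 3.3 |
| 25 points | 2.1 | 4.1 | 4.2 |
| 35 points | 2.9 | 5.7 | 5.8 |

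The mean shift is zero.

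**5. Whether this is extra variance.** Take clinic rates of 0.75 and 0.50, half the patients each, overall 0.625.
- Total variance per patient: 0.625 × 0.375 = 0.2344.
- Within clinics: (0.75 × 0.25 + 0.50 × 0.50)/2 = 0.2188.
- Between clinics: 0.125² = 0.0156.
- The two parts sum to the total.

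The ordinary standard error √(0.2344 × 2/72) = 8.07 points therefore already includes the clinic component, √(0.0156 × 2/72) = 2.1 points. The simulated SD of the arm difference was 8.06 points for 0.75/0.50 and 7.98 for 0.80/0.45. Type I error of the unadjusted test was 4.8% and 4.6%.

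**6. What adjustment could recover.** The between-clinic part of the variance is 0.0156/0.2344 = 6.7% for a 25-point gap and 0.175²/0.2344 = 13.1% for a 35-point gap. These are ceilings. After the cost of estimating clinic effects, the simulated cut in variance is about 4-12%, and smaller still for a 20-point gap.

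**7. If clinic affects the control arm only.** Relative to the trial's overall clinic mix, the SD of the shift halves: 2.1/2 = 1.0 and 2.9/2 = about 1.4 points, with a 95th percentile of roughly 2-3 points. Adjustment for clinic then gains about nothing.

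**The case against.** The best defence is that nothing here is invalid. Randomization is individual, imbalance averages to zero, and the planned test keeps its size. A reader might infer that clinic mix adds a further 2-3 points of SD to the arm difference, or that it biases the result. Steps 4 and 5 show otherwise: the mean shift is zero and the binomial standard error already counts that variance. This part of the defence stands in full.

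It is also fair that between-clinic variation in DOT is not documented. The control is described as a national-program procedure, supporter and location are settled patient by patient, and patients keep their own dose cards. Clinic as a determinant of adherence is therefore plausible but inferred, and the gaps of 20-35 points are assumptions. The chance shift is modest beside the planned 22 points, whose standard error at 62 per arm is about 7.6 points.

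A reader might further infer that one ordered set of envelopes cannot be followed at several clinics at once. The article does not support that. It does not say how envelopes are held across sites or that clinics recruit simultaneously, and stratifying by sex already implies more than one series. A condensed article may leave this to the full protocol.

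Finally, the covariate list is not closed and an analysis plan may add to it. But the article does name its stratum, its test of FEDO and its covariates, and clinic is in none of them. That part of the point survives.

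**Conclusion.** The point holds as a minor, cheap improvement. Several clinics recruit and the control is routine care, but clinic enters neither the stratification nor the analyses as described. The consequence is uncorrected chance imbalance. Its 95th percentile is about 3-6 points on the arm difference if clinics differ by 20-35 points in both arms, and about 2-3 points if a gap of 25-35 points affects the control arm only. All of this lies within the usual standard error. There is no bias, no inflation of type I error and no effect on N. The attainable gain is a variance reduction of about 4-12% under gaps of 25-35 points in both arms, and close to zero if clinics differ little or only in the control arm. The sizes rest on assumed clinic shares and adherence rates. The zero mean shift follows from individual randomization and does not depend on them.

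**What to change.** 1. Add clinic (primary versus secondary, or each clinic if numbers allow) to the a priori covariates of the logistic model, beside age and HIV status.
2. That change does not reach the comparison of mean FEDO, because a Welch t test takes no covariates. Report alongside it a prespecified linear regression of FEDO on arm, clinic and sex, with standard errors that allow unequal variances. Sex belongs there as the randomization stratum, so the statement that sex will not be adjusted for needs a matching edit.
3. According to Results, enrolment began in July 2020 and was to run through November 2020. For any patients not yet randomized, stratify by primary versus secondary clinic as well as sex. Pooling the secondary clinics avoids sparse strata.

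The cost is 1-3 degrees of freedom, a few more incomplete blocks, and a variable that should already be known for every patient. The sample size stays at 144.

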#### Blinding

Due to the nature of the interventions, it is not possible to blind study participants or research nurses and interviewers after assignment to a study arm. This is because, as part of the study procedures research, nurses must observe participants swallow their pills via VDOT, and at follow-up visits, interviewers must collect participant data regarding medication adherence. The research staff allocating participants to study groups during randomization will be blinded to the sequence. This is to minimize the likelihood that the research staff will be able to predict the next study arm assignment. Study investigators will be blinded to the allocation and any preliminary analyses before the end of the study. Only the trial statistician will be unblinded to the analyses. The data collection tools used for this purpose include information about how pill-swallowing is conducted (UC-DOT or VDOT), thus making the study group assignment obvious.

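### Envelopes handled as numbered, balanced blocks of 4 or 6 in an open-label trial let staff who can see the blocks deduce about 28% of assignments

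*Protocol article*

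**What the plan says.** The Randomization section sets the method: "Permuted block randomization with block sizes of 4 and 6 will be used to allocate participants to intervention or control groups". Allocation is 1:1 for 144 participants, stratified by sex. On balance it says "Each block will contain equal proportions of control and intervention".

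The same section then describes the handling. A block is a set of envelopes: "Within each block will be 4 or 6 sealed, opaque allocation envelopes, depending on the block size". Both levels carry numbers that follow the generated schedule. On the order of use the section says "To assign a patient to a study group, blocks will be selected in their sequential order"; the envelopes inside a block are likewise taken in turn. An envelope is opened only once the participant's details are on it. Carbon paper copies them to the card inside, and tamper-proof tape seals it.

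The section states that this makes the next assignment hard for the study team to predict. The Blinding section repeats that aim: "The research staff allocating participants to study groups during randomization will be blinded to the sequence". It also says that participants, research nurses and interviewers cannot be blinded once an arm has been assigned.

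Study Setting and Recruitment plans consecutive enrolment of every eligible patient. A research assistant assesses eligibility, and consent and the baseline questionnaire come before randomization.

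**The concern.** Mixing two block sizes protects concealment only while nobody can tell where a block begins and how long it is. Here the block is a numbered set of envelopes taken in order. Anyone who can see that set, and who remembers the arms already drawn from it, knows the remaining assignments once one arm's quota is used up. The last envelope of every block is always in that position.

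The other safeguards (opaque envelopes, tape, carbon paper, details written first) prevent early opening and swapping. They do not prevent deduction from balance.

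At stake is selection before consent. Under Eligibility Criteria some judgements are soft: whether a patient is too ill, or plans to stay in Kampala for 6 months. Patients may also enter at any visit in their first month of treatment, so deferral is possible. The primary outcome is adherence, which may depend on traits that staff can perceive. Selective entry could therefore tilt the main comparison.

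**Working it through.** The article gives no figure for predictability, so there is none to reproduce.

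**Inputs from the article.** Block sizes 4 and 6, half of each block per arm, 144 participants (all from Randomization); no blinding after assignment (Blinding).

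**Assumptions, because the article is silent.** Equal numbers of the two block sizes; staff who track every earlier assignment in the current block of that sex stratum; no allowance for an unfinished last block.

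**Step 1: block size visible.** An assignment is certain when one arm has already used its quota. List all balanced orders and average the length of the forced tail.

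- Block of 4: 6 orders; 2 have a tail of two and 4 a tail of one. Mean (2×2 + 4×1)/6 = 1.333, and 1.333/4 = 33.3%.
- Block of 6: 20 orders; 2 have a tail of three, 6 a tail of two and 12 a tail of one. Mean (2×3 + 6×2 + 12×1)/20 = 1.5, and 1.5/6 = 25.0%.
- Both agree with the closed form 2m/(m+1) for a block of size 2m: 4/3 for m = 2 and 6/4 for m = 3.
- Equal numbers of each: (1.333 + 1.5)/(4 + 6) = 28.3%, and 0.283 × 144 = 40.8, about 41 participants. The all-6 and all-4 extremes would be 36 and 48.

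**Step 2: block starts visible, sizes not.** After two of one arm and none of the other, the block could still be a 6, so nothing in a block of 4 is certain. Three of one arm can occur only in a block of 6, and from then on the rest is forced. So 1.5/10 = 15%, about 22 of 144.

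**Step 3: starts and sizes both hidden.** Take a guesser who knows only that sizes are 4 or 6, equally likely, and who updates after each assignment. In simulation 5.6% of assignments are certain in a series of 72 and 5.5% in a series of 144, about 8 of 144.

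| What enrolling staff can see | Certain in advance | Of 144 |
|---|---|---|
| Block starts and sizes | 28.3% (25.0% to 33.3%) | 41 (36 to 48) |
| Block starts only | 15% | 22 |
| Neither | about 5.5% | 8 |

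**Step 4: best guess rather than certainty.** Always guessing the arm that is behind is right 70.8% of the time in blocks of 4 and 68.3% in blocks of 6. The mix gives (0.7083×4 + 0.6833×6)/10 = 69.3%, against 50% for an unpredictable sequence. With boundaries hidden the figure is still about 69%. Every completed block is balanced, so the running imbalance in a stratum equals the imbalance inside the current block. Hiding the blocks removes most of the certainty but not this advantage.

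**The case against.** The strongest reply is that the article never says enrolling staff can see the size of a block, nor that they keep a tally. It says how blocks and envelopes are numbered and used, not how they are packaged, who holds them or how they are divided among clinics. It also says allocating staff are blinded to the sequence. The person who judges eligibility may not be the one who opens envelopes. This stands, so the 28% is conditional and has to be shown with the lower figures. Numbered blocks used in order remain the natural reading of a visible grouping, and nothing in the article rules that out.

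A second reply is that consecutive enrolment leaves little room to steer, and that a consented patient whose details are already on the envelope cannot easily be swapped. This also stands in part. What remains is selection before consent, which would breach the enrolment rule but is not physically prevented. A forced assignment can be deduced before the next patient is approached.

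Two stronger readings are tempting. One is that a quarter to a third of assignments are known before enrolment. The article does not support that: they are deducible only if staff see the blocks and track them, and the ends of that range need all blocks to be of one size. The other is that separate sequences for men and women are missing. The section states that randomization is stratified by sex, which implies a schedule per stratum; not repeating this in the envelope description is condensation.

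**Conclusion.** The handling described under Randomization undercuts the aim stated there and under Blinding. About 28% of assignments (41 of 144) can be deduced if enrolling staff see the block grouping and track assignments within the sex stratum, given equal numbers of the two sizes. The figure is 15% if they see only block starts and about 5.5% if they see neither. The visible packaging could thus raise the share of certain assignments about five-fold (28.3/5.5 = 5.1), with no benefit in return.

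These figures measure predictability, not bias. A reader might infer that the adherence comparison is biased; nothing in the article shows that, and no effect on adherence can be computed from it. The risk is real but limited by the consecutive-enrolment rule and by writing details before opening. It should be removed because doing so is cheap.

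**What to change.** Number the envelopes in one continuous series within each sex stratum, with no block number, grouping or packaging visible to enrolling staff, and withhold block sizes from them. Results has enrolment running from July through November 2020, so this can apply only to envelopes not yet used; have someone outside the enrolling team repack those. Amend the Randomization text to match. If the blocks are in fact already hidden from enrolling staff, a sentence saying so is enough.

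The cost is a small relabelling effort and some time from a person outside the team. Sample size and analysis do not change. One limit should be acknowledged: the article itself prints the block sizes, so they can be withheld only in part. The 5.5% already allows for that, because it assumes a guesser who knows the sizes are 4 or 6. The best-guess rate of about 69% would remain, so the consecutive-enrolment rule still matters.
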